| 
Criteria for evaluation:
 
Safety:
 
 
• Vital signs, physical examinations, local inspection of the infusion site
 
• Adverse event (AE) reporting
 
• Clinical laboratory testing for systemic safety parameters, including liver function and bilirubin levels, renal function, hematologic testing, and urinalysis
 
 
Clinical effect:
 
 
• IVM to measure microvascular blood flow
 
• Biomarkers of adhesion, inflammation, and downstream selectin effect in the blood
 
 
PK:
 
 
• Plasma levels of GMI-1070
 
                                                                                                                                                                                                                                                                                                                                                                                                                                                                                  |                                         |

---

|                                                                                                                                                                                                                                                                                                                                                                                                                                                                   |                                         |
|-------------------------------------------------------------------------------------------------------------------------------------------------------------------------------------------------------------------------------------------------------------------------------------------------------------------------------------------------------------------------------------------------------------------------------------------------------------------|-----------------------------------------|
| Protocol number: GMI-1070-103                                                                                                                                                                                                                                                                                                                                                                                                                              | Study drug: Intravenous GMI-1070 |
| 

• Urinary excretion of GMI-1070

                                                                                                                                                                                                                                                                                                                                                                                   |                                         |
| 
Statistical methods:
 
Due to the limited population number, descriptive statistics will primarily be used to analyze the study data. Any parameters with noticeable differences will be evaluated using an appropriate method to determine statistical significance. Due to the limited number of plasma concentrations, PK parameters will be estimated by fitting a compartmental model derived from richer datasets in healthy volunteers.
 |                                         |

## STUDY SCHEDULE

Table 1: Schedule of Assessments

|                                             | Screening within 30 days | Pre-Dose Baseline | IV GMI-1070 Dosing |                                                  |          | Post Dosing    |                |                |                       |
|---------------------------------------------|--------------------------|-------------------|--------------------|--------------------------------------------------|----------|----------------|----------------|----------------|-----------------------|
|                                             |                          |                   | 0 hrs              | 30±10 min,
2±0.25 hrs,
4±1 hrs,
8±2 hrs | 10±1 hrs | 24±3 hrs       | 48±12 hrs      |                |                       |
| Visit                                       | Before Day 1             | Day 1             | Day 1              |                                                  |          | Day 2          | Day 3          | Day 7±2        | Day 28±3  |
| Informed consent                            | ✓                        |                   |                    |                                                  |          |                |                |                |                       |
| Inclusion/exclusion criteria                | ✓                        |                   |                    |                                                  |          |                |                |                |                       |
| Assignment to dose level                    |                          | ✓                 |                    |                                                  |          |                |                |                |                       |
| Demographics                                | ✓                        |                   |                    |                                                  |          |                |                |                |                       |
| Medical history                             | ✓                        | ✓                 |                    |                                                  |          |                |                |                |                       |
| Physical examination                        | ✓            | ✓     |                    |                                                  |          | ✓  | ✓  | ✓  |                       |
| Height, weight                              | ✓                        | ✓                 |                    |                                                  |          |                |                |                |                       |
| Vital signs                                 | ✓                        | ✓                 |                    | ✓                                                |          | ✓              | ✓              | ✓              |                       |
| Electrocardiogram                           | ✓                        |                   |                    |                                                  |          |                |                | ✓              |                       |
| Biochemistry and hematology     | ✓                        | ✓                 |                    | ✓                                    |          | ✓              | ✓              | ✓              |                       |
| High sensitivity C-reactive protein (hsCRP) |                          | ✓                 |                    |                                                  |          | ✓              | ✓              | ✓              |                       |
| Pregnancy test (urine or serum)             | ✓                        | ✓                 |                    |                                                  |          |                |                |                |                       |
| Urinalysis                                  | ✓                        | ✓                 |                    |                                                  |          | ✓              | ✓              | ✓              |                       |
| Urine collection over 6 hours for PK        |                          |                   |                    | ✓                                                |          |                |                |                |                       |
| Biomarkers of adhesion sampling             |                          | ✓                 |                    | ✓                                    |          | ✓              | ✓              |                |                       |
| Plasma GMI-1070 PK sampling                 |                          | ✓                 |                    | ✓                                                |          | ✓              | ✓              |                |                       |
| IVM                                         |                          | ✓                 |                    | ✓                                                |          | ✓              |                |                |                       |
| GMI-1070 administration                     |                          |                   | ✓                  |                                                  | ✓        |                |                |                |                       |
| AEs                                         |                          | ✓                 | ✓                  | ✓                                                | ✓        | ✓              | ✓              | ✓              | ✓                     |
| Concomitant medication                      | ✓                        | ✓                 |                    | ✓                                                | ✓        | ✓              | ✓              | ✓              | ✓                     |
| Telephone contact                           |                          |                   |                    |                                                  |          |                |                |                | ✓                     |

 Telephone call only is acceptable on Day 28 ± 3. Subject should be queried concerning a positive pregnancy test since last seen.

 Full physical examination.

 Targeted physical examination.

 Complete blood count with differential, platelets, reticulocyte count, alanine transaminase, blood urea nitrogen, creatinine, electrolytes with glucose, lactate dehydrogenase (LDH), bilirubin.

 Performed only at 8 hours – hematology (complete blood count) only.

 Performed only at 4 and 8 hours.

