### **1.6.2 Pharmacokinetics**

In the single-dose study (GMI-1070-101), pharmacokinetics (PK) data showed detectable levels of drug, consistent PK parameters among subjects, and linear kinetics between groups. Plasma concentrations ( $C_{max}$ ) and  $AUC_{(0-t)}$  showed linear increases from the 2 mg/kg to the 40 mg/kg dose. Clearance (CL), renal clearance ( $CL_r$ ), apparent volume of distribution at the terminal phase ( $V_z$ ), and  $t_{1/2}$  did not change with dose. The mean value for  $CL_r$  ranged from 15.1 to 20.5 mL/minute, with an overall mean of 18.3 mL/min.  $CL_r$  was not dependent on plasma concentration. Over 90% of GMI-1070 was excreted in the urine.

In the multiple-dose study (GMI-1070-102), PK data are available for 3 dose levels: 5, 10, and 20 mg/kg. Key parameters on Days 1 and 5 for these groups ( $CL$ ,  $V_z$ , and  $t_{1/2}$ ) are consistent with those from the comparable dose level in Study GMI-1070-101.

Figure 2 below shows a semi-log graph of the single dose PK parameters from IV GMI-1070 at a range of doses from 2-40 mg/kg (GMI-1070-101 study).

[figure not shown]

Figure 2: IV GMI-1070 Pharmacokinetics with Single Dose in Volunteers: 2-40 mg/kg

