## **5 STUDY AND CONCOMITANT TREATMENTS**

### **5.1 GMI-1070**

The official product name, as indicated in the Investigator's Brochure, is 'GMI-1070 Injection, 30 mg/mL.' However, in order to allay any confusion regarding the route of administration in this protocol, the product has been referred to as 'GMI-1070.' For further details regarding the exact composition of the product, please refer to the Investigator's Brochure.

Investigational product will be supplied in vials, each containing 250 mg of liquid formulation of GMI-1070 at a 30 mg/mL concentration. Each study drug administration will occur over a period of 20 minutes from the start of the IV infusion, and will be followed by a saline flush.

The test product will be administered using 1 of the following dose regimens (2 doses total, administered at 0 and 10 ± 1 hours):

- Dose Level A, 20 mg/kg load followed by 10 mg/kg at 10 ± 1 hours
- Dose Level B, 40 mg/kg load followed by 20 mg/kg at 10 ± 1 hours
- Dose Level C, 10 mg/kg load followed by 5 mg/kg at 10 ± 1 hours
- Dose Level D, 5 mg/kg load followed by 2.5 mg/kg at 10 ± 1 hours

A written authorization (prescription/order/instruction) signed by an appropriately licensed physician, in this case the investigator, is required prior to providing any subject with investigational product.

Note: If enrollment at a site begins after other sites have enrolled in the study, the safety, PK, and blood flow information gained by early-enrolling site(s) may be used to modify dosing by later-enrolling site(s).

After Dose Level A has been administered to at least 4 subjects at one site, and this site's investigator and the Medical Monitor have determined it appropriate to proceed with another dose level as described above, a new site joining the study may proceed with either of the confirmed dose levels (Dose Level A, or the subsequent chosen dose level) if agreed by the new site's investigator and Medical Monitor.

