### **6.1.1 Screening Visit**

The Screening Visit should occur within 30 days prior to initiation of treatment. All prospective subjects will have the study explained in non-technical terms by a member of the research team or a member of the clinic staff. The nature of the drug substance to be evaluated will be explained together with potential hazards involving possible adverse reactions. Written informed consent will be obtained from each subject prior to dosing.

Subjects will have to meet all inclusion/exclusion criteria before being enrolled in the study (see Section 4).

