#### **6.2.1.3 Electrocardiogram**

A 12-lead ECG will be performed according to standard procedure at the investigational site.

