### 6.2.5 Review to Determine Next Dose Level

When 4 subjects have been studied (in any level) at the individual site, the data for these subjects will be reviewed by the investigator and Medical Monitor in order to determine the next dose to be administered. The data for the first 48 hours for each subject, as available, will be reviewed.

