**Table 3: Data Reviewed to Determine Next Dose Level**

|                        | Safety                                         | PK                                            | Effect                                        |
|------------------------|-------------------------------------------------------|------------------------------------------------------|------------------------------------------------------|
| Data to review: | Physical examination, AEs, clinical labs, vital signs | GMI-1070 plasma levels                               | IVM data                                             |
| To determine:   | If dose-limiting toxicity is seen*                    | If plasma levels are consistent with expected levels | If difference in IVM data is seen pre- and post-dose |

\*Dose-limiting toxicity is defined in Section 7.4.

Based on review of these data, and determination of the above, dosing may continue as follows using 1 of the dose levels described in this protocol:

- If dose-limiting toxicity is seen, the decision will be made based on safety data.
  - If dose-limiting toxicity is seen, and continued dosing at a lower dose level is believed to be appropriate (as determined by the investigator and Medical Monitor), the study may continue at a lower dose level.
  - If dose-limiting toxicity is seen, and continued dosing at any level is not warranted (as determined by the investigator and Medical Monitor), the study will be halted for further review of the data.
- If no dose-limiting toxicity is seen, the decision will be made based on effect data.
  - If a microvascular blood flow effect is not clearly detectable by IVM, the study may continue at the same dose to gather more data, or increase to a higher dose level.
  - If a microvascular blood flow effect is clearly detectable, the study may continue at the same dose, or decrease to a lower dose level.

Any individual site safety concerns discussed, that could have a more global impact, will be shared among all participating sites.

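### The only post-dose ECG is at Day 7 ± 2, about 85 to 183 hours after the last dose, so a transient, asymptomatic ECG effect near peak exposure would go undetected

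*Protocol*

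**What the plan says.** The Schedule of Assessments (Table 1) has one row for "Electrocardiogram", ticked at Screening and at Day 7 ± 2 and nowhere else. Section 6.2.1.3, under the Safety heading, adds only that "A 12-lead ECG will be performed according to standard procedure at the investigational site"; it gives no times. Section 6.1.1 sets the age of the pre-treatment ECG: "The Screening Visit should occur within 30 days prior to initiation of treatment".

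On dosing, Section 5.1 specifies "2 doses total, administered at 0 and 10 ± 1 hours", and "Each study drug administration will occur over a period of 20 minutes from the start of the IV infusion". Plasma PK sampling ends at 48 ± 12 hours (Sections 3 and 6.2.2).

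On the dose-level decision, Section 6.2.5 says "The data for the first 48 hours for each subject, as available, will be reviewed". The synopsis (Number of subjects) likewise refers to data through 48 ± 12 hours. Table 3 gives the safety data for that decision as "Physical examination, AEs, clinical labs, vital signs"; ECG is not among them. Section 9.2.8, by contrast, places the interim analysis after each fourth subject at a site has completed the study.

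**The concern.** The primary objective is safety in adults with sickle cell disease, and Section 2.1 presents this trial as the first evaluation of the drug in such patients. Table 1 gives the other main safety measures a same-day baseline and follow-up close to exposure. Vital signs are taken predose, at 30 minutes, 2, 4 and 8 hours, and at 24 and 48 hours. Physical examination and laboratory tests are done predose and at 24 and 48 hours, with a blood count at 8 hours as well. The ECG has neither a Day 1 baseline nor a measurement during exposure, and no reason is given for the difference.

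The trial's own grading scale (Appendix 1) includes ECG-defined findings that cause no symptoms, such as minor T-wave flattening at Grade 1 and asymptomatic ST and T wave changes at Grade 2. Questioning about adverse events and measuring pulse and blood pressure would not be expected to reveal these. If they occurred on the dosing day and resolved, no record of them would exist at any dose level, and the 48-hour review could not take them into account.

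**Working it through.** The protocol states no interval between dosing and ECG, so there is no figure to reproduce. The check is visit-window arithmetic.

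**Inputs.** Table 1 labels the dosing day Day 1, the 24-hour visit Day 2 and the 48-hour visit Day 3, so Day d is nominally (d − 1) × 24 h after the first dose. The second dose starts at 9 to 11 h and runs for 20 minutes (Section 5.1). The ECG visit can fall on Day 5 to Day 9. The last PK sample and the last dose-review data come at 48 ± 12 h, hence by 60 h. Screening is up to 30 days before dosing.

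**ECG time after the last dose** = (d − 1) × 24 − time of the second dose.

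| Visit | Hours after first dose | Second dose at | Hours after second dose |
|---|---|---|---|
| Day 5 (earliest) | 96 | 11 h | 85 |
| Day 7 (nominal) | 144 | 10 h | 134 |
| Day 9 (latest) | 192 | 9 h | 183 |

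Measured from the end of the second infusion, the minimum is 85 − 20/60 = 84.7 h. Clock times barely alter this: assuming first doses between 07:00 and 09:00 and a Day 5 ECG between 08:00 and 17:00, the minimum ranges from 84 to 95 h.

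**Gap to the PK and dose-review data.** 96 − 60 = 36 h at the narrowest; 144 − 48 = 96 h nominally. No ECG coincides with a scheduled drug-level measurement. This needs no assumption about half-life.

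**Age of the comparator.** Up to 30 days before Day 1, plus 8 days to Day 9: the two ECGs can be 38 days apart.

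**Illustration of drug remaining.** The text gives no human half-life or volume of distribution, so volume is an assumption here. Section 1.6.2 gives a mean renal clearance of 18.3 mL/min and says "Over 90% of GMI-1070 was excreted in the urine".

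- Renal clearance: 18.3 × 60/1000 = 1.10 L/h. Total clearance lies between 1.10 L/h (all renal) and 1.10/0.9 = 1.22 L/h.
- Half-life = ln 2 × V/CL, treating the body as one compartment.
- Fraction left after 85 h = 2^(−85/half-life).

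| Assumed V | CL | Half-life | Fraction left at 85 h |
|---|---|---|---|
| 5 L | 1.22 L/h | 2.8 h | effectively nil (about 30 half-lives) |
| 20 L | 1.10 L/h | 12.6 h | 0.94% |
| 30 L | 1.10 L/h | 18.9 h | about 4% |

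**Where an ECG could fit.** Subjects are in clinic for up to 11 h on Day 1. If timed from the start of the 20-minute infusion, the 30 ± 10 minute assessment falls 0 to 20 minutes after the loading infusion ends, close to its peak.

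**The case against.** The strongest reply is that sparse ECG monitoring was a reasonable choice. Section 1.5.1 reports two hERG assays at up to 10 mg/mL without a signal and no apparent QT effect in monkeys given up to 75 mg/kg in a 14-day study. Section 1.6.1 reports no clinically significant ECG findings in 72 volunteers (54 active, 18 placebo), whose regimens included a 40 mg/kg load followed by 20 mg/kg for 2 days, at least as much as this trial's Dose Level B. Section 2.1 describes the starting exposure as substantially lower than in the earlier studies. Acute cardiac effects are also not unwatched: vital signs and adverse events are recorded through dosing, and Section 7.1 allows further tests after an event. Most of this stands, and it lowers the weight of the point. But those volunteers did not have sickle cell disease, their data were still blinded when summarised, and none of it makes a Day 7 recording informative about the hours of exposure.

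A reader might infer more than the documents support:

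- *That an ECG component of the safety objective cannot be answered.* The protocol defines no such component. The objective is general safety, and ECG is absent from the synopsis safety criteria, Table 3 and the safety analyses named in Section 9.1.
- *That the trial yields no usable ECG evidence.* A Day 7 ECG compared with Screening can show a persistent change.
- *That no ECG could ever reach a dose decision.* That follows from Section 6.2.5 and the synopsis. Under Section 9.2.8 the review would come after the Day 28 follow-up, when the Day 7 ECG already exists, although Table 3 would still not list it.
- *That no drug is left by then.* That depends on the assumed volume.

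**Conclusion.** The point holds in a limited form. The only post-dose ECG falls about 85 to 183 h after the last dose, at least 36 h beyond the last PK sample and the data that Section 6.2.5 uses for the dose decision, and is compared with a Screening ECG up to 30 days older than the first dose. What goes undetected is specific: a transient ECG effect near peak exposure, without symptoms or a vital-sign change, in the first sickle cell patients treated.

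This conclusion rests on the visit windows and on nominal clock times. The fraction of drug remaining is only illustrative: under 1% at 85 h for an assumed volume up to 20 L, about 4% at 30 L. The existing volunteer and nonclinical data make this a worthwhile low-cost correction, not grounds for saying that the trial fails its primary objective. Separately, Sections 6.2.5 and 9.2.8 disagree on when the dose review happens.

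**What to change.** In Table 1, move the Day 7 ± 2 ECG to Day 1, alongside the 30-minute or 2-hour assessments after the first infusion. Move the Screening ECG to predose baseline if it is not needed for eligibility. Sections 4.2 and 4.3 contain no ECG criterion, but an investigator may rely on it when judging whether a medical condition excludes a subject; if so, keep it at Screening and accept the older comparator, or add a predose recording. Add ECG to the safety column of Table 3. Reconcile Sections 6.2.5 and 9.2.8 so that the timing of the dose review is stated once.

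The number of ECGs is unchanged and subjects are already on site. The costs are the loss of the late ECG, and so of the chance to see a persistent or delayed change, unless the Day 7 recording is kept as an extra one; and a protocol amendment, since Section 10.4.3 gives adding or deleting a safety-monitoring test as an example requiring sponsor, investigator and IRB approval. A single uncontrolled ECG in groups of 4 remains limited evidence, but it would be taken when the drug is present. If the sponsor prefers the present timing, the protocol should say what the Day 7 ECG is for.
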